## **1 Protocol summary**

Title: Safety of artesunate-amodiaquine combined with methylene blue or with primaquine for falciparum malaria treatment in African children: A randomised controlled trial.

Design: Mono-center, two arms, open randomised controlled non-inferiority study in children with uncomplicated falciparum malaria in Burkina Faso.

Phase: Phase II.

Objectives: The primary objective of this trial is to investigate the safety of artesunate (AS) – amodiaquine (AQ) - methylene blue (MB) compared to AS – AQ - primaquine (PQ) in young children with uncomplicated falciparum malaria in Burkina Faso

Population: Children aged 6-59 months with uncomplicated falciparum malaria from Nouna Hospital in north-western Burkina Faso.

Sample size: 100 patients (50 per study arm).

Treatment: The group AS-AQ-MB will receive once daily a fixed dose AS-AQ formulation combined with once daily MB (15 mg/kg) over a three days period. The control group will

## **Artesunate – Amodiaquine - Methylene blue – Phase II Clinical Trial Protocol**

receive once daily a fixed dose AS-AQ over three days combined with a single dose of PQ on day 2 (0.25 mg/kg).

Endpoints: Primary endpoint is the haemoglobin value on day 7 compared to baseline. Secondary endpoints are adverse events (AE), adequate clinical and parasitological response (ACPR) rate (PCR-corrected for recrudescence), as well as gametocyte prevalence and density.

Study duration and dates: The study will be implemented during the rainy season of the year 2016 from June until November.

## 2 Abbreviations

|      |                                                |
|------|------------------------------------------------|
| MB   | Methylene blue                                 |
| AQ   | Amodiaquine                                    |
| AS   | Artesunate                                     |
| PQ   | Primaquine                                     |
| ACT  | Artemisinin-based combination therapy          |
| SAE  | Serious adverse event                          |
| AE   | Adverse event                                  |
| SSA  | Sub-Saharan African                            |
| CRF  | Case Report Form                               |
| CRSN | Nouna Health Research Centre                   |
| ACPR | Adequate clinical and parasitological response |
| ETF  | Early treatment failure                        |
| LCF  | Late clinical failure                          |
| LPF  | Late parasitological failure                   |

## Definitions

| Term                         | Definition                                                                                                                                                                                                                                                                                                                                                                                                                                                                                               |
|------------------------------|----------------------------------------------------------------------------------------------------------------------------------------------------------------------------------------------------------------------------------------------------------------------------------------------------------------------------------------------------------------------------------------------------------------------------------------------------------------------------------------------------------|
| Baseline values              | Directly after the written informed consent a blood sample will be taken for the baseline measurements (laboratory baseline values).                                                                                                                                                                                                                                                                                                                                                                     |
| Age                          | The age is calculated using the date of informed consent and date of birth. If the day of the birth date is unknown, it is set to 15. If day and month are missing the 1 st of July is assumed to be the date of birth.                                                                                                                                                                                                                                                                       |
| D0, D1, D2, D3, D7, D14, D28 | 
For the definition of study days a modification of the latest WHO definition is used (WHO 2003).
 
D0= calendar day of the first treatment, D1= first calendar day after the calendar day of first treatment. These definitions are used for the endpoints ETF, LCF, LPF, ACPR, gametocyte prevalence, density and infectivity, and fever or parasite clearance time. D14 and D28 are defined as the 14th and 28th day after first drug intake (tolerance +/- 2 days).
 |
| ETF                          | 

• Danger signs or severe malaria on D1, D2 or D3 + parasitemia

                                                                                                                                                                                                                                                                                                                                                                                           |

## **Artesunate – Amodiaquine - Methylene blue – Phase II Clinical Trial Protocol**

| Term                               | Definition                                                                                                                                                                                                                                                                                                                                                    |
|------------------------------------|---------------------------------------------------------------------------------------------------------------------------------------------------------------------------------------------------------------------------------------------------------------------------------------------------------------------------------------------------------------|
|                                    | 

• Parasitemia on D2 > D0 count irrespective of axillary temperature

• Parasitemia on D3 > 25% D0 count irrespective of axillary temperature

                                                                                                                                                     |
| LCF                                | 

• Development of danger signs or severe malaria after D3 in the presence of parasitemia, without meeting any of the criteria of ETF

• Presence of parasitemia + axillary temperature <math>\geq 37.5^{\circ}\text{C}</math> on any day from D4 to D28, without previously meeting any criteria of ETF

 |
| LPF                                | 

• Presence of parasitemia on any day from D7 to D28 + axillary temperature <math>< 37.5^{\circ}\text{C}</math>, without previously meeting any of the criteria of ETF

                                                                                                                                      |
| ACPR                               | 

• No parasites on D28 irrespective of axillary temperature without previously meeting any of the criteria of ETF, LCF or LPF

                                                                                                                                                                                  |
| Recrudescence                      | Re-emerging of the same P. falciparum strain from D7 to D28 according to PCR genotyping                                                                                                                                                                                                                                                                |
| Reinfection                        | New infection from D3 to D28 according to PCR genotyping                                                                                                                                                                                                                                                                                                      |
| AEs                                | The adverse event (=AE) defined in chapter 9 is used. Blue urine is expected for all children in the MB treatment group. Only AEs after initiation of study treatment will be tabulated.                                                                                                                                                                      |
| SAE                                | The definition of serious adverse event (SAE) is given in chapter 9                                                                                                                                                                                                                                                                                           |
| Haemolysis                         | Any drop in haemoglobin (Hb) of $> 2.5$ g/dl within 24 hours                                                                                                                                                                                                                                                                                                  |
| Severe acute haemolysis            | Hb $\leq 5$ g/dl or received blood transfusion according to clinical judgement of study physician.                                                                                                                                                                                                                                                            |
| Severe acute neurological disorder | Acute change in consciousness
$\geq 2$ convulsions                                                                                                                                                                                                                                                                                                         |

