### Study procedures:

100 children aged 6-59 months with uncomplicated falciparum malaria will be included into the study. All study children will be followed up for 28 days.

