## **Artesunate – Amodiaquine - Methylene blue – Phase II Clinical Trial Protocol**

AQ; 9.0-17.9 kg: 50 mg AS + 135 mg AQ; >17.9 kg: 100 mg AS + 270 mg AQ), given over a three days period. In addition, on day 2 the children of this group will receive a single dose of 0.25 mg/kg PQ (Sanofi, India) using four weight groups (6.0 – 8.9 kg: 2 mg PQ; 9.0-12.9 kg: 3 mg PQ; 13.0-16.9 kg: 4 mg PQ; >17.0 kg: 5 mg PQ).

All children having fever (temperature  $\geq 38.5^{\circ}\text{C}$ ) will receive standard doses of paracetamol (= acetaminophen; 10 mg/kg every 6 hours) until symptoms subside.

Study children developing severe malaria during the trial will be admitted to the Nouna hospital and treated with quinine according to national guidelines. Study children developing uncomplicated malaria recrudescence or reinfection or who show asymptomatic parasitological failure during follow-up between day 7 and day 28 will be treated with artemether-lumefantrine according to national guidelines.

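### LCF and LPF do not exclude each other, so one child can count in both failure rates; separately, a narrow D3 gap in the failure rules needs reconciling with the cited WHO standard

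*Protocol*

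**What the plan says.** The failure categories stand in the Definitions table that follows protocol section 2.

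- **ETF** has three criteria: "Danger signs or severe malaria on D1, D2 or D3 + parasitemia"; a D2 count above the D0 count; and a D3 count above "25% D0 count irrespective of axillary temperature".
- **LCF** has two criteria. The first is "Development of danger signs or severe malaria after D3 in the presence of parasitemia, without meeting any of the criteria of ETF", with no temperature condition. The second is parasites with an axillary temperature of at least 37.5 °C "on any day from D4 to D28, without previously meeting any criteria of ETF".
- **LPF** is "Presence of parasitemia on any day from D7 to D28" with a temperature below 37.5 °C, "without previously meeting any of the criteria of ETF".
- **ACPR** requires no parasites on D28 and none of ETF, LCF or LPF before.

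Section 4 (Definition of outcomes) reports ETF, LCF and LPF as separate PCR-corrected rates, and ACPR as a further PCR-corrected secondary endpoint. Section 5 states: "All study children will be followed up for 28 days". Under Description of the treatments in section 6, children with recurrent malaria or asymptomatic parasitological failure "during follow-up between day 7 and day 28 will be treated with artemether-lumefantrine". Section 8 says that these outcomes follow the WHO 2003 standard protocol, while the Definitions table announces a modification of WHO only for the definition of study days.

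**The concern.** Rates reported side by side as ETF, LCF, LPF and ACPR are read as a partition in which each child has one outcome. The LCF and LPF rows do not deliver that, because each rules out ETF only. The ACPR row shows that a chained exclusion was available. Follow-up continues to D28 after re-treatment, so parasites seen after the second antimalarial can be classified again as written. At stake are the split between clinical and parasitological late failure and the additivity of the published rates.

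The second matter is the boundary between D3 and D4. The rule combining fever with parasites begins on D4. Every child has a smear and a temperature at the scheduled D3 visit, whereas D4 to D6 have only unscheduled visits. A febrile, parasitaemic child on D3 can therefore pass as a success. The protocol does not say whether that is intended.

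**Working it through.** **Inputs.** The rules are those of the Definitions table. The denominator is 50 per arm (sections 1 and 6). The plan states no expected rate for ETF, LCF, LPF or ACPR, so there is no such rate to reproduce. The 50 itself does reproduce from the haemoglobin comparison: 2 × [1.1722 × (1.960 + 0.842) / 0.7]² = 44.02, rounded up to 45; 45 / 0.90 = 50.

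**Step 1: apply the rules literally to test profiles.** Temperatures and counts are illustrative. Counts are relative to D0, and days not mentioned are clear.

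| Profile | ETF | LCF | LPF | ACPR |
|---|---|---|---|---|
| A. D3: 10%, 38.2 °C, no danger signs | no | no | no | yes |
| B. Same finding on D4 (unscheduled visit) | no | yes | no | no |
| C. D3: 30%, 38.2 °C | yes | no | no | no |
| D. D3: 10%, 38.2 °C, danger signs | yes | no | no | no |
| E. D14 febrile with parasites, D28 afebrile with parasites | no | yes | yes | no |
| F. D14 afebrile with parasites, D28 febrile with parasites | no | yes | yes | no |
| G. D14 danger signs with parasites at 36.9 °C | no | yes | yes | no |

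E and F are double flags over two visits. G is a double flag at one visit: the first LCF criterion has no temperature condition, and a temperature below 37.5 °C satisfies LPF.

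**Step 2: effect of the overlap.** Let L be the number of children with a late failure and k the number flagged as both. Then LCF count + LPF count = L + k. Before PCR correction and with all children assessable, the four rates sum to 100% + k/n.

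- k = 1, n = 50: 1/50 = 2.0 points, so the sum is 102%.
- k = 1, n = 45 (assuming the planned 10% loss, 50 × 0.90): 1/45 = 2.2 points.

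E, F and G are non-ACPR however the overlap is resolved, and each is one failing child. ACPR and total failures do not move.

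**Step 3: effect of the D3 gap.** Profiles C and D show that D3 fever with parasites is already ETF when the count exceeds 25% of D0 or danger signs are present. Only profile A escapes. If it counted as ETF, each such child who later clears would move from ACPR to ETF, by 2.0 points at n = 50 or 2.2 at n = 45. The documents give no frequency. Assuming 1 to 5 such children per arm, the shift is 1/50 to 5/50 = 2 to 10 points, or 1/45 to 5/45 = 2.2 to 11.1 points.

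**The case against.** Several objections have force.

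- **The overlap is only a labelling matter.** A reader might infer that it makes ACPR wrong or adds failures to the study regimen. It does neither. ACPR excludes all three failure types, and a child flagged again after re-treatment has already failed once.
- **Re-treatment and PCR correction limit it.** Re-treatment should make a second flag less likely. Section 8 ties genotyping to the day parasites reappear, not to every later positive smear. Both may reduce cases E and F. Neither can prevent case G, and no text stops a second classification.
- **Counting rules belong in the analysis plan.** An analysis plan is announced and may settle the hierarchy. But the protocol does not leave the exclusions open: it states them, and as stated they overlap.
- **The D3 boundary may be deliberate.** Tolerating a falling count on D3 and counting febrile parasitaemia from D4 is coherent, and any day-based rule treats adjacent days differently. A reader might infer that WHO 2003 requires D3 fever with parasites to be ETF. The documents cannot show that, because the WHO text is not reproduced. What stands is that the table declares a modification for study days only, so a departure elsewhere, if this is one, is undeclared.
- **Harm to the arm comparison is not shown.** A reader might infer that the gap favours methylene blue, because section 3 describes it as slow against asexual parasites. That statement cites a study whose title in the reference list describes monotherapy in semi-immune adults. Here both arms receive AS-AQ. A difference between arms is possible, not demonstrated.

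**Conclusion.** The concern holds in limited form. As written, LCF and LPF can both apply to one child, over successive visits or at a single visit. The two rates may therefore be misallocated and sum to more than the number of children with late failure, by 2 percentage points per affected child at 50 per arm. How many children would be affected is unknown. ACPR and total failures are not changed by this overlap.

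The D3 gap is separate and narrow: fever with parasites on D3, a count at or below 25% of D0, and no danger signs. It is the only route found here by which ACPR could be raised and ETF lowered. Whether such a child ought to be a failure cannot be settled from the documents; the Definitions table and section 8 need to be reconciled. The general reading that fever with parasites on D3 is never a failure is not supported.

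The endpoints are secondary and analysed descriptively (section 9). The primary haemoglobin analysis and the sample size are unaffected. One caution: the ETF row runs across a page break. No lost line is visible, but the original table should be checked.

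**What to change.** In the Definitions table:

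1. State that each child is classified once, at the first failure.
2. Let LPF exclude both ETF and LCF, and let LCF exclude an earlier LPF.
3. State that LCF takes precedence when both are met at the same visit. Excluding only previous failures would leave case G unresolved.
4. State that parasitaemia after re-treatment is not classified again.
5. For febrile parasitaemia on D3 at or below 25% of the D0 count without danger signs, either add it to the outcome definition or declare its omission as an intended departure, so that the table agrees with the WHO 2003 reference in section 8.

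These changes concern outcome classification only and alter no treatment rule. They cost a few lines and need no new data, since smears and temperatures are already taken at these visits. If the D3 gap is closed, the ETF and ACPR rates may look slightly less favourable.

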### **3 Introduction and study rationale**

#### **Malaria**

Malaria remains the globally most important parasitic disease (Greenwood et al. 2005). The greatest burden of malaria is in sub-Saharan African (SSA) where it has been estimated that 40% of fever episodes are caused by malaria and where children regularly experience several malaria episodes each year (Greenwood et al. 2005, Müller et al. 2001). Most malaria deaths occur in young children of rural SSA areas with little access to health services (Snow et al. 1999, Greenwood et al. 2005, Müller et al. 2003).

Treating malaria with a combination of effective drugs has become a new paradigm in malaria control, with the particular aim to delay and possibly reverse the development of drug resistance through different mechanisms (Nosten and Brasseur 2002). Artemisinin-based combination therapy (ACT) has proved highly effective and has now become the standard first-line treatment for falciparum malaria in all endemic areas (International Artemisinin Study Group 2002, WHO 2015). As resistance against artemisinin compounds has recently started to emerge in South-East Asia, there is a clear need to develop alternative malaria drug combinations (Noedl et al. 2008). Adding another anti-malarial with a short half-life such as methylene blue to standard ACT could be a strategy to prevent artemisinin resistance development (Müller et al. 2009). Moreover, adding a gametocytocidal drug to ACT reduces the probability of transmission of *P. falciparum* parasites including drug-resistant parasites. Such effects are particularly important for malaria treatment in countries or regions aiming at malaria elimination (WHO 2015).

#### **Methylene blue**

Methylene blue (MB) is a water-soluble dye used for a long time in industry and medicine. In humans, the drug is rapidly and widely distributed throughout the body (Schirmer et al. 2003; Wainwright & Amaral 2005; Schirmer et al. 2011). The drug is well absorbed from the gastrointestinal tract and partly monodemethylated to azure B in hepatocytes. Maximal plasma concentrations are reached 2 hours following oral administration, and the plasma half-life is about 20 hours (Walter-Sack et al. 2009). Renal excretion of MB and azure B (in oxidised blue or reduced uncoloured forms) is the main elimination pathway (DiSanto and Wagner 1972, Peter et al. 2000). Known side effects of MB are a bitter taste, a mild and self-limiting dysuria, and a blue colouration of the urine (Schirmer et al. 2011, Müller et al. 2013). In contrast to its obvious toxicity when applied intravenously at doses >10 mg/kg, the oral application of MB is usually well tolerated. Even oral doses up to 17 g (5x 100-200 mg per day) were well tolerated

in early malaria studies (Guttmann and Ehrlich 1891). In a historical case series of 40 children with malaria from Brazil, oral doses of 20-50 mg/kg per day given over days to weeks have also been well tolerated (Ferreira 1893).

MB has been used against malaria for more than 100 years (Guttmann und Ehrlich 1891, Ehrlich 1913). Its further use against human malaria is not well documented, thus only observational data supported its efficacy, particularly in malaria cases found refractory to quinine (Ehrlich 1913, Dale 1956). MB is a registered drug in most countries for a number of indications such as treatment of methaemoglobinaemia (Schirmer et al. 2011). It is also used for the prevention of ifosfamid-induced encephalopathy in human cancer treatment. For these indications, MB is usually given intravenously 2-6 times per day at a dose of 1-2 mg/kg (Mansuri and Lurie 1993, Zulian et al. 1995, Aeschlimann et al. 1998, Pelgrims et al. 2000). The use of MB in malaria treatment may also be beneficial in preventing methaemoglobinaemia and thus tissue hypoxia (Anstey et al. 1996). Another potentially clinically relevant effect is an increase in blood pressure in patients with septic shock due to a blockade of NO-dependent guanylate cyclase (Galili et al. 1997).

The interest in MB as an antimalarial drug was reactivated when *P. falciparum* glutathione reductase was identified as a new drug target (Färber et al. 1998, Sarma et al. 2003, Schirmer et al. 2003). MB inhibits the glutathione reductase of the malaria parasite and less the human enzyme; like its major catabolite, azure B, MB is a subversive redox-cycling substrate, and similar to 4-aminoquinolines it seems to also interact with the polymerization of haem to hemozoin (Kanzok et al. 2000, Davioud-Charvet et al. 2001). In the food vacuole reduced MB inhibits metHb degradation by reducing MetHb to Hb. Indeed there seem to be even more but not yet fully understood mechanisms how the pluripotent MB interacts with the parasite which makes resistance development rather unlikely (Wainwright & Amaral 2005). MB has been shown to be very effective in inhibiting *P. falciparum* in culture and this has been confirmed in the mouse model (Vennerstrom et al. 1995).

In a series of clinical studies recently conducted in Burkina Faso, oral MB (4-24 mg/kg/day given for three days) was shown to be safe and effective in the treatment of uncomplicated falciparum malaria when combined with other antimalarials (Mandi et al. 2005, Meissner et al. 2005, Meissner et al. 2006), but acted rather slowly against the asexual parasites (Bountogo et al. 2010). Also a single oral dose of 500 mg MB was well tolerated in healthy German adults (Walter-Sack et al. 2009). Finally, a synopsis of data from more than 1000 children with and without glucose 6-phosphate-dehydrogenase (G6PD) deficiency, which were enrolled into clinical trials with MB in West Africa showed no clinically relevant drop of

